### Interventions

2.7

#### NIBS_RHB_

2.7.1

A specialized rehabilitation protocol for postsurgical ACL recovery will be implemented. This protocol, grounded in the latest clinical guidelines (43–45), will be structured into four distinct phases: i) post-surgical recovery (weeks 0–5); ii) strength and neuromuscular control (weeks 6–12); iii) running, agility, and landings (weeks 13–24); and iv) return to sport activity (after week 24). The program will encompass 72 sessions scheduled three times a week over a 24-week period. Strength training will be the primary focus of all phases. To ensure optimal patient progress, regular assessments will be conducted with advancement to subsequent recovery phases based on the specific criteria. A schematic representation of the exercise protocol will be employed during rehabilitation (Table 2).

**Table 2 T2:** Phased rehabilitation protocol following ACL reconstruction: objectives, progression criteria, and recommended exercises.

Phase		Weeks	Objectives	Progression criteria	Recommended exercises
Post-surgery recovery	PHASE 1.1	0–2	• Achieve fully extend the knee • Reduce inflammation • Activate the quadriceps • Full extension (0°) • Active quadriceps contraction	• Full extension (0°) • Active quadriceps contraction • Quadriceps Lag Test	• Straight leg raise (SLR): flexion, extension, abduction and adduction • Peripheral joint mobilization • Isometric quadriceps at 90°–60° • Gait training • Inflammation management: cryotherapy + compression
	PHASE 1.2	3–5		• Extension 0° • Contralateral flexion −10° • Absence of inflammation (stroke test)	Strength: • Squat (0°–60°) • Hamstring Curl • Step Up → Step Up + running technique • Lumbo-pelvic strengthening: Clamshell, Side-Lying Leg Raise Bilateral/Unilateral, Hip Hike Balance: • Progression from bilateral to single leg stance • Stationary cycling >100°
Strength and motor control	PHASE 2.1	6–8	• Restore knee strength • Restore muscle strength • Execute Single Leg Stance with proper technique	• Absence of edema • Absence of pain/edema post-exercise • Full Range of Motion (ROM) • Normal gait pattern	• Leg press, Hamstring curl, Hip abduction and adduction, Knee extension (90°–45°), Air squat with band, Deadlift • Single leg squat (SLS) progression • Progression of unilateral balance exercises to include perturbations
	PHASE 2.2	9–12		• Absence of instability episodes • 10 SLS at 60° • Functional evaluation • Quadriceps index >80% • Hamstring index >80% • Gluteus medius >80%	Previous phase + • Bilateral plyometrics in partial load • Bilateral plyometrics in full load • Submaximal training in sport-specific sagittal plane movements
Running, agility, and landings	PHASE 3.1	12–16	• Attain optimal performance in jump exercises • Complete the prescribed plyometric, agility, and running program • Regain full strength and balance capabilities	• Achieve pain-free and inflammation-free running • Functional evaluation • Quadriceps/hamstring/Gluteus medius strength >90% • Q/H RATIO >66% • Hop test >90%	Exercises (continue progressive strength training + plyometric, agility, and running block). • Bilateral sagittal plane plyometrics: broad jump, box jump, tuck jump, hop over line. • Unilateral sagittal plane plyometrics: pogo hops, lunge jump, bounding run. • Sagittal plane agility: ladder drills, forward and backward, figure-eight, deceleration, etc. • Running: adaptation protocol + running protocol (week 1)
	PHASE 3.2	16–24		• Absence of pain or inflammation • Pain-free activity performance • Appropriate movement pattern execution	Exercises (continue progressive strength training + plyometric, agility, and running block). • Frontal plane bilateral plyometrics: lateral hop over the line/hurdles, tuck jumps over the line/hurdles, etc. • Frontal plane unilateral plyometrics: lateral hop over the line/hurdles, tuck jumps over the line/hurdles, etc. • Frontal plane agility: zig-zag run, side shuffle/shuffle run, cone drills, crossover step, lateral ladder drills. • Running: running protocol (weeks 2–7).
Return to play	PHASE 4	+24	• Melbourne Return to Sport Score of 95+ • Patient demonstrates comfort, confidence, and readiness to return to sports • ACL injury prevention program implemented	• Functional evaluation • Quadriceps/hamstrings/gluteus medius strength index >90% • Q/H RATIO >70% • Hop test >90% RTP • Month 7: unrestricted training • Month 9/10 return to competition • Functional evaluation: • Quadriceps/hamstrings/gluteus medius strength index >95% • Q/H RATIO >75% • Hop test >95%	• Exercises (continue progressing strength block + plyometrics and multiple agility) • Multiple plyometrics: drop jump + rapid change of direction, 90° and 180° jumps, etc. • Multiple agility: box and start drill, lateral shuffle over the hurdles, etc.

Furthermore, the tDCS device from Ionclinics will be used in the study. The device will be applied during the early stage of rehabilitation, specifically during activation, as the exercises required will be less demanding, less intricate, and more appropriate for this intervention. The treatment plan includes 16 sessions over an 8-week period, with two sessions each week. Each session will administer a continuous current of 2 mA for 20 min. The setup comprises two electrodes (a red anode and a black cathode) and two sponge pads with conductive gel, all incorporated into a helmet tailored to the patient. Electrode placement will adhere to the international 10–20 system for tDCS (46). The primary motor cortex (M1) will be the focus of stimulation, with the anode placed at either C3 or C4, corresponding to the hemisphere contralateral to the injured leg, to target the affected motor area. The cathode will be positioned at the opposite supraorbital area, either Fp1 or Fp2. This placement ensures that stimulation is applied to the motor cortex controlling the injured limb, which is critical for modulating cortical excitability and enhancing the neuromuscular control. The tDCS stimulation will be applied prior to this early rehabilitation phase to ensure proper monitoring and to maximize the safety and efficacy of the intervention*.* The tDCS stimulation will be applied prior to this early rehabilitation phase. Specifically, during the Post-Surgery Recovery Phases 1.1 and 1.2, as well as the Strength and Motor Control Phase 2.1.

#### SHAM_NIBS_ _+_ _RHB_

2.7.2

The device will be configured to produce an upward gradient for 30 s, identical to that used in the experimental group, followed by a downward gradient for another 30 s. Consequently, the control group will feel a tingling sensation on their scalp similar to that of the experimental group. This stimulation will occur for a total of 60 s, which is insufficient to induce changes in cortical excitability (47). Studies have demonstrated that this approach effectively ensures patient blinding (48).

### Outcomes

2.8

#### Baseline characteristics

2.8.1

To ensure accurate data collection for the study and monitor the patient's progress during rehabilitation, various measurements will be recorded. These will include the patient's sex, age, body mass index, athletic discipline, injury date, surgical procedure date, type of graft employed in the reconstructive surgery, time since surgery and hand/foot dominance. The study will also include measurements of knee circumference to assess volume at 5 and 10 cm above the patella's upper edge for the thigh and 5 and 10 cm below the patella's lower edge for the calf muscle. Finally, the extent of muscular arthrogenic inhibition and the patient's subjective pain perception will be evaluated.

#### Primary outcome

2.8.2

##### Electromyographic muscle activation

2.8.2.1

The primary outcome of this study will be the recorded electromyographic activity of eight (four on each leg) target muscles. Wireless surface electromyography (EMG) and force sensors (MuscleLab, Stathelle, Norway) connected to a 12-channel EMG amplifier (model ML6EMG01, MuscleLab, Stathelle, Norway) will be used to record muscle activity. The electrodes utilized will be the Lessa Pediatric Electrode model (30 mm diameter). The placement of electrodes will follow the SENIAM guidelines, which are part of the European Concerted Action under the BIOMED II program for noninvasive muscle assessment using surface electromyography (49). Both lower extremities will be recorded, and the placement order by channel number will be as follows: channel 1, vastus medialis (VM) (right); channel 2, rectus femoris (RF) (right); channel 3, vastus lateralis (VL) (right); channel 4, biceps femoris (BF) (right); channel 5, VM (left); channel 6, RF (left); channel 7, VL (left); and channel 8, BF (left). The muscle activity sampling rate will be 1 kHz, with each session lasting between 5 and 60 s, depending on the specific exercise.

The patients will be instructed to perform each movement with the maximum possible contraction and as quickly as possible to achieve the highest peak force (50). The patient will perform three familiarization repetitions at submaximal intensity at the beginning of each repetition (51). Assessments will first be conducted on the healthy extremity, followed by testing on the surgically repaired knee. Patients will attempt three maximum voluntary isometric contractions (MVIC), each lasting 5 s, with a 30-s rest interval between each repetition (52). A 10-min rest period will be allowed between each position to prevent the influence of fatigue on the results and to ensure optimal recovery. Additionally, the patient will receive both visual and verbal feedback (e.g., “come on”, “go ahead”) to encourage maximal effort (51).

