### Sample size

2.6

The required sample size was determined using GPower® software (Franz Faul, Universität Kiel, Kiel, Germany), version 3.1.9.2. A preliminary sample of 46 subjects, divided into two groups of 23 participants each, was established for the intervention design. The primary variable (EMG output) was used for statistical analysis through repeated measures ANOVA. Cohen's effect size was set at 0.357 based on a previous study examining using surface EMG recordings as their primary outcome (41). The calculation incorporated a statistical power of 0.95, an alpha level of 0.05, and two intervention groups. To account for potential dropouts during treatment follow-up (estimated at 15%), an additional 3 participants were added to each group. This resulted in a total of 54 participants, with 27 per group. The chosen effect size, exceeding 0.357, is classified as “moderate” (42). If a greater percent of participants does not follow their planned treatment protocol (dropouts, non-adherence to treatment, or missing results), an “intention-to-treat” analysis will be conducted.

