##### EMG analysis

2.8.2.2

Once the data are recorded, they will be stored on a hard drive in Comma-Separated Values (. csv) files. Signal analysis will be performed using MATLAB software (R2025a) (Mathworks Inc., Natick, USA). Data will be collected using a smooth-data function. Initially, a fourth-order Butterworth bandpass filter ranging from 20 to 400 Hz will be applied to process the signal. The signal will then undergo rectification or Root Mean Square (RMS) analysis by dividing the measurement section into 100 segments. Based on the exercise, we will extract segments lasting between 3 and 30 s (for analysis). The central 30 s in the resting position will be used as the baseline EMG. For dorsal flexion, plantar flexion, and the gamified approach, the central 5 s of work will be considered, and the mean RMS will be quantified for each exercise. For tests of maximum isometric contraction of knee flexion and knee extension, the central 3 s and maximum RMS will be used. In addition, the peaks of each signal will be calculated using the MATLAB “findpeaks” function, and the relationship between the signal peaks and individual muscles will be determined, which will allow the order of contraction to be established. Finally, the activation frequency of each recording will be calculated. The highest value recorded during the three trials will be selected and normalized based on each patient's body mass index to remove the influence of body mass, thereby enabling a comparison between them.

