##### Analysis of the outcome measures

2.10.2.2

A per-protocol analysis will be performed in accordance with the CONSORT guidelines for reporting randomized controlled trials. The Kolmogorov–Smirnov test will be utilized to verify the normality assumption, and the Levene test will be used to evaluate the homogeneity of variances. To examine the effects of tDCS combined with exercise-based rehabilitation on patients undergoing ACL reconstruction, repeated measures ANOVA will be applied, with experimental groups as factors and Bonferroni corrections for *post hoc* analysis. Comparisons within and between groups for both primary and secondary outcomes will assess time, group, and interaction effects. Results will be expressed as mean differences (MD) with 95% confidence intervals (CI95%). The effect size (ES) will be calculated using Cohen's d coefficient. All statistical analyses will be conducted using SPSS 24 software (IBM Inc., Chicago, Illinois, USA). If there are participant dropouts or if the statistical power is below 80%, an intention-to-treat analysis will be implemented (78).

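### The primary EMG outcome covers eight muscles with no muscle, leg, task, feature or effect named as decisive, while the sample size assumes one EMG variable at alpha 0.05

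*Protocol article*

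**What the plan says.** Section 2.8.2.1 of the protocol article defines the primary outcome: "The primary outcome of this study will be the recorded electromyographic activity of eight (four on each leg) target muscles". The channels are vastus medialis, rectus femoris, vastus lateralis and biceps femoris on each side.

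Section 2.8.2.2 describes what is extracted:
- Mean RMS for three tasks: "For dorsal flexion, plantar flexion, and the gamified approach, the central 5 s of work will be considered".
- Maximum RMS for two tasks: "For tests of maximum isometric contraction of knee flexion and knee extension, the central 3 s and maximum RMS will be used".
- Signal peaks, related across muscles, "which will allow the order of contraction to be established".
- A frequency measure: "Finally, the activation frequency of each recording will be calculated".

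Section 2.10.2.2 gives the analysis: "repeated measures ANOVA will be applied, with experimental groups as factors and Bonferroni corrections for" post hoc analysis. It adds: "Comparisons within and between groups for both primary and secondary outcomes will assess time, group, and interaction effects".

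Section 2.6 sizes the trial on one variable, called EMG output, in a repeated measures ANOVA: "The calculation incorporated a statistical power of 0.95, an alpha level of 0.05, and two intervention groups". This gives 46 participants (23 per group), raised to 54 for dropout.

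**The concern.** A primary outcome has to identify the one result on which the confirmatory claim stands. Here the definition lists channels, and the section that should narrow them adds tasks and features instead. The only multiplicity control covers post hoc comparisons inside an ANOVA. It does not reach across muscles, tasks, features or effects.

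The sample-size section and the outcome section therefore describe different endpoints: one variable tested once at 5%, and a family of variables with no rule for combining them. A favourable result in one channel could be presented as the primary finding, and nothing in the document prevents it. The stated power is also tied to no identifiable test.

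**Working it through.** **1. The plan's own figure.** Inputs from section 2.6: effect size 0.357 (read here as Cohen's f), alpha 0.05, power 0.95, two groups, N = 46. The number of repeated measures m, the correlation rho between them and the effect being powered are not given. In the G*Power form, the noncentrality is f²·N·m/(1+(m−1)·rho) for the group effect and f²·N·m/(1−rho) for the interaction. At an assumed rho of 0.5 and m from 2 to 5, the required N is 64 to 80 for the group effect and 16 to 28 for the interaction. So 46 cannot be reproduced without further assumptions. It is unverifiable rather than shown to be wrong, and it belongs to one variable only.

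**2. Smallest reading of the family.** One task, one feature, one treatment effect, each channel tested at 5%. For K independent tests the chance of at least one false positive is 1 − 0.95^K:
- K = 8: 1 − 0.95^8 = 0.337.
- K = 4 (operated leg only): 1 − 0.95^4 = 0.185.

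EMG channels are correlated, so these are upper values. With equicorrelated two-sided normal tests (correlations assumed, since the documents give none):

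| Correlation | 8 channels | 4 channels |
|---|---|---|
| 0 | 34% | 18.5% |
| 0.3 | 30% | 17% |
| 0.5 | 25% | 16% |
| 0.7 | 19% | 13% |
| 0.9 | 12% | 9% |

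**3. One step wider.** Eight channels in both maximal-contraction tasks make 16 tests: 1 − 0.95^16 = 0.560 if independent, 26% at correlation 0.7 and 15% at 0.9.

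**4. Power of candidate repairs at N = 46 (23 per arm).**

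Splitting alpha over eight channels gives 0.05/8 = 0.00625. With m = 3 and rho = 0.5 (assumed):
- Group effect: noncentrality 0.357²·46·3/2 = 8.79; power falls from 83% to 54%.
- Interaction: noncentrality 0.357²·46·3/0.5 = 35.18; power falls from above 99.9% to 99.6%.

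For a single-visit comparison between arms, f = 0.357 corresponds to d = 2 × 0.357 = 0.714:
- Unadjusted, at alpha 0.05: 66%.
- Adjusted for baseline, the effective d is 0.714/√(1−r²). For an assumed baseline correlation r of 0.3, 0.5 or 0.7 it is 0.748, 0.824 or 1.000, and power is 70%, 78% or 91%.
- Reaching 95% unadjusted would take 52 per arm.

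The same f describes a different size of treatment difference in each of these tests, so the powers show sensitivity to the choice of contrast. They do not rank the contrasts.

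**The case against.** A reader might infer that every muscle, task and feature is tested at 5% for three effects and that any significant result would count, which leads to error rates close to 100%. The documents do not support that reading:
- The 5% level appears only in the sample-size section, and no success rule is stated.
- The resting recording is a baseline, not an endpoint task.
- Mean and maximum RMS belong to different tasks, so they do not multiply.
- A gamified contraction is described as a procedure only under the secondary outcome on cortical excitability (section 2.8.3.4).
- Order of contraction is a sequence between muscles, not an obvious per-channel ANOVA variable. Section 2.8.2.2 does not say that each derived signal is a primary endpoint.
- A time effect is expected after surgery in both arms. A true effect is not a false positive, so the fair count is group and interaction, or interaction alone.
- Section 2.4 says that testing is bilateral so that comparisons can be made within a participant. On that reading the uninjured leg is a comparator and four channels remain.

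A second tempting claim is that correcting over eight muscles would cost too much power. That holds for the group effect and the single-visit comparison, but not for the interaction under the assumptions above.

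It can also be said that a testing hierarchy is usually left to a statistical analysis plan, which is not shown. That is fair for the hierarchy. It does not cover the choice of primary outcome, which this document fixes as eight undifferentiated channels. These objections reduce the size of the problem, but they do not supply a decisive variable.

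**Conclusion.** The point holds in a limited form. The protocol names no decisive muscle, leg, task, feature or effect for its primary outcome, and its only multiplicity correction does not cover that choice. The 5% error rate used for sizing is therefore not secured for the primary claim. The error is about 12% to 34% for eight channels and about 9% to 18.5% for the four operated-leg channels. Those figures rest on three assumptions: any one significant channel is read as success, each is tested at 5%, and correlations lie between 0.9 and 0. They count one task, one feature and one effect, so further tasks or features would push them up. The missing definition is read directly from the text. The inflation is conditional on the success rule, on which the text is silent. This should be corrected before unblinding, because it concerns the trial's only confirmatory outcome.

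**What to change.** Before unblinding, amend the protocol and the registry entry as follows:
- Name one primary EMG variable: one task, one feature, the operated leg, and either one muscle or a pre-specified average of the quadriceps channels.
- Name one treatment contrast. Preferably this is the group-by-time interaction of the planned repeated measures ANOVA. A baseline-adjusted difference between arms is the alternative.
- State that a time effect alone is not evidence for tDCS.
- Make the other muscles, tasks and features and the uninjured leg secondary with Holm adjustment, or exploratory.
- Restate the power for the chosen contrast, giving the number of measurements and the correlation assumed.

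This costs wording, a registry update and a new power statement, with no new measurement. There are two downsides. The remaining measures lose confirmatory status. The stated 95% power may also not carry over, as the 66% unadjusted and 70% to 91% baseline-adjusted figures for a single visit show.

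Baseline adjustment also needs the EMG recording that Table 1 marks at t1. Section 2.4 lists assessments only from one month after surgery, so the two places must be reconciled first.

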##### EMG analysis

2.8.2.2

Once the data are recorded, they will be stored on a hard drive in Comma-Separated Values (. csv) files. Signal analysis will be performed using MATLAB software (R2025a) (Mathworks Inc., Natick, USA). Data will be collected using a smooth-data function. Initially, a fourth-order Butterworth bandpass filter ranging from 20 to 400 Hz will be applied to process the signal. The signal will then undergo rectification or Root Mean Square (RMS) analysis by dividing the measurement section into 100 segments. Based on the exercise, we will extract segments lasting between 3 and 30 s (for analysis). The central 30 s in the resting position will be used as the baseline EMG. For dorsal flexion, plantar flexion, and the gamified approach, the central 5 s of work will be considered, and the mean RMS will be quantified for each exercise. For tests of maximum isometric contraction of knee flexion and knee extension, the central 3 s and maximum RMS will be used. In addition, the peaks of each signal will be calculated using the MATLAB “findpeaks” function, and the relationship between the signal peaks and individual muscles will be determined, which will allow the order of contraction to be established. Finally, the activation frequency of each recording will be calculated. The highest value recorded during the three trials will be selected and normalized based on each patient's body mass index to remove the influence of body mass, thereby enabling a comparison between them.

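### Contraction order is read from EMG peaks, which do not measure activation onset; within the central 3 s of a 5 s maximal hold the recovered order is at chance

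*Protocol article*

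**What the plan says.** The maximal task is described in section 2.8.2.1 of the protocol article: "Patients will attempt three maximum voluntary isometric contractions (MVIC), each lasting 5 s, with a 30-s rest interval between each repetition". Four muscles are recorded on each leg, and "The muscle activity sampling rate will be 1 kHz".

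Section 2.8.2.2 then sets out the processing. The signal is band-passed at 20-400 Hz and either rectified or reduced to RMS by "dividing the measurement section into 100 segments". The windows are fixed by task: "For tests of maximum isometric contraction of knee flexion and knee extension, the central 3 s and maximum RMS will be used"; "For dorsal flexion, plantar flexion, and the gamified approach, the central 5 s of work will be considered".

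After the amplitude measures, the section adds that "the peaks of each signal will be calculated using the MATLAB “findpeaks” function" and that "the relationship between the signal peaks and individual muscles will be determined, which will allow the order of contraction to be established". It names no onset criterion. It does not say which peak is used (first, largest or all), whether the search runs on the rectified signal or the RMS, or whether it runs on the cropped window or the whole recording.

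**The concern.** Order of contraction means which muscle becomes active first. In a sustained hold the EMG rises at the start and then fluctuates around a plateau. Where its peaks fall on that plateau depends on those fluctuations and not on when the muscle switched on. A window taken from the middle of the hold also leaves out the only part of the record that carries the information.

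The article does more than leave a detail open: it asserts that the peaks will establish the order. The Introduction frames the trial around neuromuscular control. Among the EMG features listed in section 2.8.2.2, contraction order is the one that relates the timing of one muscle to another. A result reported under that name could present noise as a change in recruitment, or miss a real one.

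**Working it through.** The article gives no figure for contraction order, so there is nothing to reproduce. The check has three steps.

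**1. What the window removes.** Hold 5 s, window the central 3 s: (5 − 3)/2 = 1 s is dropped at each end. With four muscles and a lag of up to 100 ms between successive onsets, the last muscle starts 3 × 100 = 300 ms after the first. All four onsets therefore precede the window. With an assumed rise constant of 80 ms, the last muscle has risen for at least 1,000 − 300 = 700 ms when the window opens, and the remaining shortfall is exp(−700/80) = exp(−8.75) ≈ 0.0002. The window sees only plateau.

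**2. Chance level and time resolution.** A full order of four muscles is right by chance with probability 1/4! = 1/24 = 4.2%; a pair, 50%. If RMS is used, 100 segments give bins of 3 s/100 = 30 ms or 5 s/100 = 50 ms, so shorter lags cannot be resolved. If the signal is only rectified, this limit does not apply.

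**3. Simulation of order recovery.** From the article: four muscles, 5 s hold, 1 kHz, fourth-order 20-400 Hz Butterworth filter, 100-segment RMS for the peak rules. Assumed, because the article gives no values: noise-like EMG, lag of 10-100 ms between successive muscles, rise constant 80 ms, 10% slow fluctuation of drive, and an optional early burst of 50% or 100% above plateau. There were 400 runs per cell. Entries are % of full orders correct, with % of pairs correct in brackets.

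| Record and rule | 10 ms | 20 ms | 50 ms | 100 ms |
|---|---|---|---|---|
| Central 3 s, largest peak | 4.3 (49.9) | 5.0 (50.9) | 4.3 (48.6) | 4.5 (51.0) |
| Central 3 s, first peak | 4.8 (52.4) | 3.7 (50.2) | 4.0 (49.2) | 4.5 (49.0) |
| Full 5 s, largest peak, no burst | 5.8 (52.1) | 3.5 (48.0) | 3.5 (50.5) | 2.2 (50.5) |
| Full 5 s, largest peak, 50% burst | 4.5 (50.3) | 3.5 (52.7) | 7.0 (53.1) | 8.3 (58.3) |
| Full 5 s, largest peak, 100% burst | 5.5 (54.5) | 7.7 (55.5) | 14.2 (65.5) | 28.5 (76.1) |
| Full 5 s, first peak above half maximum, no burst | 8.3 (55.6) | 12.0 (65.4) | 27.3 (79.4) | 63.5 (92.8) |
| Full 5 s, first peak above half maximum, 50% burst | 8.5 (57.5) | 10.7 (66.4) | 33.0 (82.3) | 66.2 (94.0) |
| Threshold onset, uncropped with prior rest | 98.0 (99.7) | 100 (100) | 100 (100) | 100 (100) |

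Simulation error at chance is √(0.0417 × 0.9583/400) ≈ 1.0 percentage point, so values between about 2% and 6% do not differ from 4.2%.

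A separate simulation used other assumptions: 30 ms lag, 200 ms ramp, amplitude signal-to-noise ratio of 20, amplitude decline of 0%, 20% or 40%, and 1,500 trials per setting. The segment with the largest RMS recovered 3-4% of full orders and 48-51% of pairs, on the central 3 s and on the full 5 s. Threshold onset recovered about 96% and 99%.

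**The case against.** The strongest reply is that this tests one reading of a short sentence. The article refers to each signal, so the order analysis is not confined to maximal holds. It does not fix the window, the signal or the peak. Patients are told to contract fast, which makes an early burst plausible, and the peak-finding routine returns local maxima, not only the highest. On a full record a first-peak rule does carry information, up to 64-66% of full orders at a 100 ms lag. The peak rules above were run on RMS; rectification alone would remove the bin limit, and its effect on the full-record figures was not tested. Settings of this kind often sit in a fuller protocol.

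Most of this stands as a limit on scope. A reader might infer that the contraction-order measure is essentially random whatever is done, or that any group difference in it must be noise. The article does not support that, because it does not commit to the cropped window or to the largest peak. A reader might also infer that the trial's measure of neuromuscular control fails. The article never gives contraction order that role: it is introduced as an addition after the amplitude measures, and the sample size in section 2.6 rests on EMG output. Pure noise in it would cost power without biasing the randomised comparison.

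The core is not answered. The article states positively that peaks will establish the order, and every contraction window it names is a central one. The gamified contraction in section 2.8.3.4 is also a hold, at 30% of maximum, so the same reasoning reaches beyond the maximal tests. The rule that does best, the first peak above half maximum on the whole record, appears nowhere in the article.

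**Conclusion.** The point holds in a limited form. Peak timing is not a measure of activation onset, and section 2.8.2.2 uses it as one.

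- **Central 3 s of a 5 s maximal contraction:** recovery is at chance (3.7-5.0% of full orders, 49-52% of pairs) at every lag examined and for either peak rule. This follows from the window and hardly depends on the assumed signal properties.
- **Full record, largest peak:** at or near chance unless there is a strong early burst and lags are long (14% at 50 ms and 29% at 100 ms with a 100% burst).
- **Full record, first peak above half maximum:** better than chance but unreliable at short lags (8-33% at 10-50 ms).

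The full-record figures rest on assumed lags, rise time, burst and noise. The onset figures of 96-100% come from clean, sharp simulated onsets and are best read as an upper bound. Mean and maximum RMS do not depend on this step and are unaffected. This is a correctable fault in an added descriptor, not a threat to the primary amplitude comparison.

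**What to change.** Replace the peak rule in section 2.8.2.2. Compute contraction order from EMG onset on the uncropped, band-passed and rectified recording. Define onset as the first sustained crossing of the resting mean plus a fixed multiple of the resting SD, with the multiple and the minimum duration set in advance. The resting recording already planned supplies the mean and SD. Keep the central 3 s for amplitude only.

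The method needs a quiet interval before each contraction, and the article does not say that the recordings contain one. Add an instruction to start each recording before the effort begins. Where recordings hold no pre-contraction interval, drop the contraction-order claim, since a separate resting file cannot restore a missing rise.

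The cost is a sentence or two in the protocol, a few lines of MATLAB and an earlier start to each recording. No extra visits or tests are needed.
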